**Methods/Design:**

This study is a pragmatic, open label randomised trial.

A total of 150 patients (age 18–80 years) visiting the general practitioner with complaints suggestive of trochanteric pain syndrome will be allocated to receive local corticosteroid injections or to receive usual care. Usual care consists of analgesics as needed. The randomisation is stratified for yes or no co-morbidity of low back pain, osteoarthritis of the hip, or both. The treatment will be evaluated by means of questionnaires at several time points within one year, with the 3 month and 1 year evaluation of pain and recovery as primary outcome. Analyses of primary and secondary outcomes will be made according to the intention-to-treat principle. Direct and indirect costs will be assessed by questionnaires. The cost effectiveness will be estimated using the following ratio: CE ratio = (cost of injection therapy minus cost of usual care)/(effect of injection therapy minus effect of usual care).

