### Questionnaires

The primary outcome measurements will be experienced recovery at 3 months and at 1 year, measured on a 7-point Likert scale (1 = fully recovered till, 7 = worse than ever) and severity of pain during the last week measured with a numeric rating scale (0 = no pain, 10 = worst conceivable pain). Medical consumption of the patient (e.g. medication, visits to the GP or physiotherapist, hospital treatment and diagnostic tests) will be measured as direct cost. The PRODISC questionnaire will be used to measure the cost effectiveness and will measure the indirect costs, expressed in work staff absence and loss of productivity in paid work, or loss of productivity in not-paid work [12]. The WOMAC (Western Ontario and McMaster University Osteoarthritis Index) is recommended by the Osteoarthritis Research Society for use in clinical trials in people with hip osteoarthritis to measure pain and disabilities [13]. The HOOS (hip disability and osteoarthritis outcome score) [14] is developed as an extended version of the WOMAC, to evaluate the whole domain of patient-relevant outcome in young and active patients and is recently validated in the Dutch language [15]. The HOOS consists of 5 subscales; Pain, other Symptoms, Function in daily living (ADL), Function in sport and recreation (Sport/Rec) and hip-related Quality of life (QOL). Both the WOMAC and HOOS will be used in this study. We use the EuroQol (EQ5D) as instrument to measure quality of life [16].

Finally, we ask the patients who received an injection, to report any side effects of the injection. Table 1 shows the timing of measurements.

**Table 1 T1:** Timing of study questionnaires

	baseline	6 weeks	3 months	6 months	9 months	12 months
Severity of pain: VAS (1–10)	x	x	x	x	x	x
Experienced recovery: Likert (1–7)		x	x	x	x	x
HOOS including WOMAC	x	x	x	x	x	x
Prodisq + medical consumption	x		x	x	x	x
EQ 5 D	x		x	x	x	x
Side effects of injection		x	x	x	x	

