### Data analyses

Difference between the groups in the primary outcome will be analysed based on the basis of the "intention-to-treat" principle. Differences in continuous outcome measures between the groups will be analysed with linear regression techniques and differences in dichotomous outcomes (recovery dichotomised to totally recovered or almost totally recovered versus slightly recovered and less) will be analysed with logistic regression techniques. Baseline differences between the groups will be assessed and checked whether these influence the outcome of the study. Baseline variables that change the outcome by 10% or more will be regarded as confounders and will therefore be added to the regression models.

Regression models will also be used to study effect modification of comorbidity. A cost-effectiveness analyses will be performed from a social and a patient perspective, looking at differences in direct and indirect health care cost between the two groups.

If the trial does not show a difference in disease parameters (VAS and WOMAC) and quality of life (EuroQol) between the groups, the analysis will be reduced to a cost minimisation analysis. This form of analysis evaluates the efficacy of treatment based solely on direct and indirect costs. If the study does find a positive difference in disease parameters and/or quality of life in the injection group, a cost-effectiveness ratio can be determined.

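### The economic analysis falls back to costs alone when VAS, WOMAC and EuroQol show no difference, without an equivalence criterion and without recovery in the trigger

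*Protocol article*

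**What the plan says.** The Data analyses section of the protocol article first announces a cost-effectiveness analysis from two perspectives and then makes its form depend on the clinical result.

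- Trigger: "If the trial does not show a difference in disease parameters (VAS and WOMAC) and quality of life (EuroQol) between the groups".
- Consequence: "the analysis will be reduced to a cost minimisation analysis". The article adds: "This form of analysis evaluates the efficacy of treatment based solely on direct and indirect costs".
- Other branch: "If the study does find a positive difference in disease parameters and/or quality of life in the injection group, a cost-effectiveness ratio can be determined".

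The Methods/Design part of the Abstract attaches no such condition: "The cost effectiveness will be estimated using the following ratio", followed by the cost difference divided by the effect difference.

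The Questionnaires section names the primary outcomes. One is recovery: "The primary outcome measurements will be experienced recovery at 3 months and at 1 year, measured on a 7-point Likert scale". The other is pain on a 0 to 10 scale, which Table 1 and the trigger call VAS. The Sample size section uses recovery at three months only. The Discussion ranks the osteoarthritis questionnaires, which include the WOMAC, as secondary.

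**The concern.** Cost minimisation is justified when the effects of two treatments are known or shown to be equal. The trigger asks only that a difference has not been shown. The article describes two-sided testing and regression for differences. It attaches no margin or confidence-interval criterion to the rule, so an inconclusive result would be handled like a demonstration of equality. The effect estimate and its uncertainty would then drop out, and the cheaper arm could be preferred while the data still allow a worthwhile gain or loss in health.

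The trigger also leaves out recovery. The trial could meet its design target on recovery and still be costed as though the arms had the same effect.

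Two problems of wording add to this. The Abstract states the ratio without condition, whereas Data analyses makes it conditional. And Data analyses does not say explicitly what follows a difference favouring usual care.

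Cost-effectiveness is a stated aim in the Abstract and Background, so one of the trial's headline conclusions is at stake.

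**Working it through.** **Inputs from the article (Sample size section).** Recovery 45% versus 70%, two-sided alpha 0.05, power 0.80, dropout 10%, 75 per group.

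**Reproducing the stated 75.**
- Pooled two-proportion formula, mean rate 0.575: n = [1.96·√(2·0.575·0.425) + 0.8416·√(0.45·0.55 + 0.70·0.30)]² / 0.25² = 60.2, so 61 per arm.
- With continuity correction: (60.2/4)·[1 + √(1 + 4/(60.2·0.25))]² = 67.95, so 68 per arm.
- With dropout: 68/0.9 = 75.6, or 68·1.1 = 74.8, which gives 76 or 75. The stated figure is reproduced.

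**Precision on a continuous outcome.** Evaluable per arm: 75·0.9 = 67.5, taken as 67. The article gives no SD for VAS, WOMAC or EuroQol, so differences are in SD units, for one unadjusted comparison.
- 95% CI half-width: 1.96·√(2/67) = 0.34 SD.
- Difference detectable with 80% power: (1.96 + 0.8416)·√(2/67) = 0.48 SD.

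**Could this trial show equal effect?** Two one-sided 5% tests, true difference zero. The margins are assumptions.

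| Margin (SD) | n per arm for 80% power | Power at 67 per arm |
|---|---|---|
| 0.2 | 429 | 0% |
| 0.3 | 191 | 7% |
| 0.4 | 108 | 50% |
| 0.5 | 69 | 79% |

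**How often would a real benefit reach the cost-only branch?** The rule needs no difference on all three scales. Three normal z-statistics were simulated, each with mean d/√(2/67) and common correlation r, and the proportion of trials with every |z| < 1.96 was counted. Here d and r are assumptions, and d is the same on all three scales.

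| True benefit d (SD) | r = 0 | r = 0.3 | r = 0.5 | r = 0.7 |
|---|---|---|---|---|
| 0.2 | 49% | 55% | 59% | 64% |
| 0.3 | 20% | 28% | 34% | 40% |
| 0.5 | 0.5% | 2% | 4% | 6.5% |
| 0.65 | all under 1% | | | |

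The last row is the design effect on a latent normal scale: Φ⁻¹(0.70) − Φ⁻¹(0.45) = 0.524 + 0.126 = 0.65.

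**Effect of baseline adjustment.** All three scales are measured at baseline. With an assumed baseline correlation of 0.5, d is divided by √(1 − 0.25). At 0.3 SD and r from 0.3 to 0.7, the chance falls from 28-40% to 18-29%.

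**Positive on recovery, yet costed on costs alone.** Recovery is set at the design values of 45% and 70% (power 0.84 at 67 per arm), with r from 0.3 to 0.7 among all four outcomes. The share of trials with significant recovery and all three scales non-significant is 43-49% if the scales differ by 0.2 SD, 20-26% at 0.3 SD and 6-9% at 0.4 SD.

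**The case against.** Several points on the other side have force.

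- **Test not named.** The rule speaks of a difference not being shown and names no test, p-value or time point. This stands: non-significance is an inference. It is the natural one, because on point estimates some difference would almost always exist and the cost-only branch would hardly ever apply. On either reading the rule needs rewriting.
- **Primary outcomes.** A reader might infer that the primary outcomes are ignored. The article does not support that. Pain is in the trigger, and recovery has its own logistic regression under intention-to-treat. Only the economic trigger omits recovery.
- **Result favouring usual care.** A reader might infer that no analysis exists if injection does worse. That goes too far. Both the Abstract and Data analyses announce a cost-effectiveness analysis without a condition on sign, a result favouring usual care is still a difference, and the second branch permits a ratio without forbidding one elsewhere. What remains is missing explicit wording.
- **Size.** Quoting only true effects of 0.2 to 0.3 SD would be selective. If all three scales moved as much as the design effect on recovery, the switch would be reached wrongly in under 1% of trials. Baseline adjustment, or counting a difference at any of the repeated visits, would lower the chances further. This stands, so the full range is shown.
- **Detail left to a fuller plan.** The choice of health-economic tools is commonly settled outside a condensed article, and its absence here is no fault. The switch itself, however, is stated in the article.

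**Conclusion.** The concern holds for the economic analysis. The rule, on its natural reading, treats non-significance on three scales as equal effect in a trial whose interval reaches about 0.34 SD either side of the estimate. It also omits the one outcome that determined the sample size.

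How often this would mislead is uncertain. For a true benefit equal on all three scales it ranges from under 1% of trials at 0.65 SD to 64% at 0.2 SD. Those figures rest on assumed effects, assumed correlations of 0 to 0.7, unadjusted single comparisons and the non-significance reading. The objection to the rule does not depend on where in that range the truth lies: with 67 per arm, equivalence could be shown with about 80% power only for a margin near 0.5 SD.

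The point should be fixed, but it is confined to the economic objective. The primary efficacy analyses, the randomisation, the sample size and the data collection are untouched.

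**What to change.** Delete the switch to cost minimisation. State that incremental cost and incremental effect will be estimated jointly in all cases, whatever the sign or significance of the effect, with their joint uncertainty (for example by bootstrap). Include recovery alongside EQ-5D among the effect measures. Bring the Abstract and Data analyses into line, so that both describe the same unconditional analysis and a result favouring usual care is plainly covered.

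The cost is revised wording and modest extra analysis. No new data are needed: Table 1 already schedules EQ-5D, the cost questionnaires and pain at baseline, 3, 6, 9 and 12 months, and recovery at each of those follow-up visits. The change should be made before outcome data are analysed.

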## Discussion and current status

In this study design we compare two types of therapy which are frequently used in general practice. This study design is appropriate to estimate effectiveness and cost-effectiveness of the injection therapy. We choose to use a pragmatic study design and are thus not able to study specific effects of the injection with corticosteroids. A distinction between placebo effect of the injection and specific effects of the corticosteroids is therefore not possible.

The study is executed in general practice and may therefore not apply to patients in secundary care.

No disease specific questionnaires are available for this disorder. Therefore generic outcome measures (recovery and pain severity) were chosen as primary outcome measures. However, region specific questionnaires for osteoarthritis were included as secondary outcome measures. These questionnaires allow us to analyse subscales like for instance the WOMAC pain and the WOMAC function; subsequently osteoarthritis specific questions on stiffness (WOMAC stiffness) can validly be omitted.

Patients included in our trial have symptoms of TPS solely, or have these symptoms in co-occurrence with low-back pain or osteoarthritis of the hip. To include patients with such co-morbidity maybe questionable because the TPS may be due to such morbidity. Therefore injection therapy for TPS in such morbidity possibly shows different effectiveness. We chose to include these patients because in common practice these patient also receive injection therapy. We, however, used a design in which we stratify for co-morbidity or not.

The current status of the study is that of a total of the 80 GPs participating in the study. However, until now only 43 GPs included 90 patients. The total study population is expected to be recruited by February 2008. The first short-term results (3 months of folluw-up) will be available at mid-2008.
